## Abstract

**Background:**

Neurological injuries remain the leading cause of death in comatose patients resuscitated from out-of-hospital cardiac arrest (OHCA). Adequate blood pressure is of paramount importance to optimize cerebral perfusion and to minimize secondary brain injury. Markers measuring global cerebral ischemia caused by cardiac arrest and consecutive resuscitation and reflecting the metabolic variations after successful resuscitation are needed to assist a more individualized post-resuscitation care. Currently, no technique is available for bedside evaluation of global cerebral energy state, and until now blood pressure targets have been based on limited clinical evidence. Recent experimental and clinical studies indicate that it might be possible to evaluate cerebral oxidative metabolism from measuring the lactate-to-pyruvate (LP) ratio of the draining venous blood. In this study, jugular bulb microdialysis and immediate bedside biochemical analysis are introduced as new diagnostic tools to evaluate the effect of higher mean arterial blood pressure on global cerebral metabolism and the degree of cellular damage after OHCA.

**Methods/design:**

This is a single-center, randomized, double-blinded, superiority trial. Sixty unconscious patients with sustained return of spontaneous circulation after OHCA will be randomly assigned in a one-to-one fashion to low (63 mm Hg) or high (77 mm Hg) mean arterial blood pressure target. The primary end-point will be a difference in mean LP ratio within 48 h between blood pressure groups. Secondary end-points are (1) association between LP ratio and all-cause intensive care unit (ICU) mortality and (2) association between LP ratio and survival to hospital discharge with poor neurological function.

**Discussion:**

Markers measuring cerebral ischemia caused by cardiac arrest and consecutive resuscitation and reflecting the metabolic changes after successful resuscitation are urgently needed to enable a more personalized post-resuscitation care and prognostication. Jugular bulb microdialysis may provide a reliable global estimate of cerebral metabolic state and can be implemented as an entirely new and less invasive diagnostic tool for ICU patients after OHCA and has implications for early prognosis and treatment.

**Trial registration:**

ClinicalTrials.gov (ClinicalTrials.gov Identifier: NCT03095742). Registered March 30, 2017.

**Electronic supplementary material:**

The online version of this article (10.1186/s13063-019-3397-1) contains supplementary material, which is available to authorized users.

## Background

In comatose patients resuscitated from out-of-hospital cardiac arrest (OHCA), anoxic brain injuries remain the leading cause of death [1]. The overall mortality, though improved considerably over the last decade, continues to be significant and in most countries is as high as 90% [2, 3]. Despite successful resuscitation and admission to an intensive care unit (ICU), the in-hospital mortality is reported to be 30–50% [4, 5]. Functional favorable outcomes among OHCA survivors remain low, and global anoxic brain injury represents a major mechanism of long-term disability [6, 7]. During the post-resuscitative phase, the most significant clinical challenge is to limit secondary brain injury. Targeted temperature management (TTM) targeting 33–36 °C may mitigate cerebral ischemia–reperfusion injury and is recommended in current international guidelines [8–10]. However, managing post-cardiac arrest patients is far more complex than TTM alone, and brain-directed therapies include maintenance of normal oxygenation, ventilation, hemodynamic support to optimize cerebral perfusion, and glycemic control [10, 11].

Reduced cerebral blood flow (CBF), which is mainly dependent upon mean arterial blood pressure (MAP), can result in brain ischemia and enhance secondary brain injury after cardiac arrest. Arterial hypotension may exacerbate brain injury following cardiac arrest because of ongoing cerebral hypoperfusion. Cerebral autoregulation is frequently impaired after cardiac arrest [12, 13], and brain perfusion declines when the MAP falls below 80 to 100 mm Hg. Thus, the generally recommended MAP of above 65 mm Hg [11] to reverse the acute shock state may be inadequate to maintain adequate cerebral perfusion.

When considering blood pressure goals, clinicians should balance the metabolic needs of an ischemic brain with the potential for overstressing a decompensated heart. Post-cardiac arrest myocardial dysfunction, caused by coronary infarction and ischemia–reperfusion injury, is common after CA and resuscitation. Excessive vasopressor use may cause increased afterload and augmented oxygen consumption of the heart, thereby aggravating the myocardial damage [14]. High-dose vasopressor use has been associated with increased mortality [15].

Randomized control trials addressing specific MAP targets in post-resuscitation care have not yet been performed. This study addresses strategies for neuroprotection and will randomly assign a total of 60 unconscious resuscitated patients after OHCA in a double-blinded one-to-one fashion to low (mean 63 mm Hg) or high (mean 77 mm Hg) MAP target.

Secondary brain injury processes throughout the post-resuscitation period remain complex and involve numerous pathophysiological pathways that result from secondary ischemia and reperfusion injury. These include cerebral edema, inflammation, unbalanced CBF, and mitochondrial dysfunction [16]. Markers measuring global cerebral ischemia and reflecting the metabolic variations after resuscitation are needed for a more individualized post-resuscitation care and target-driven therapy to improve patient outcome [17, 18].

Microdialysis (MD) allows biochemical variables of the extracellular interstitial fluid to be monitored continuously and provides data on substrate supply and metabolism at the cellular level in the brain [19]. Cerebral energy metabolism is strictly aerobic, and the parameters monitored (glucose, pyruvate, lactate, glutamate, and glycerol) are closely linked (Fig. 1) [20]. Under clinical conditions, the cerebral cytoplasmic redox state is conventionally evaluated from the lactate-to-pyruvate (LP) ratio obtained from intracerebral MD and bedside biochemical analysis. Compromised energy metabolism will cause a shift in the cytoplasmic redox state that is immediately reflected in an increase of the LP ratio [21].

**Fig. 1 Fig1:**
[figure not shown]
Schematic diagram of cerebral metabolism. Schematic illustration of cerebral intermediary metabolism is shown with a focus on the glycolytic pathway and its relation to glycerol, glycerophospholipids, and the citric acid cycle. *Abbreviations*: *α-KG* α-ketoglutarate, *DHAP* dihydroxyacetone-phosphate, *F-1,6-DP* fructose-1,6-diphosphate, *FFA* free fatty acid, *G-3-P* glycerol-3-phosphate, *GA-3P* glyceraldehyde-3-phosphate. Underscored metabolites are obtained at the bedside with enzymatic techniques.

Clinical MD monitors the supply of glucose and its metabolism via glycolysis to pyruvate, which under oxidative conditions enter the tricarboxylic acid cycle. During hypoxic conditions or if mitochondrial function is compromised, pyruvate is metabolized to lactate. Therefore, the LP ratio is used as a marker of aerobic versus “anaerobic” metabolism not requiring oxygen [22]. High LP ratio is considered a robust indicator of anaerobic metabolism and the redox status of the tissue and is an independent predictor of mortality and unfavorable outcome in traumatic brain injury among patients monitored with MD [23–27]. An increased LP ratio could result from a failure of oxygen delivery (ischemic hypoxia) or no ischemic causes (e.g., mitochondrial dysfunction) [28]. An increase in the LP ratio in the presence of low pyruvate (and low oxygen pressure) indicates ischemia. In contrast, an increase in LP ratio in the presence of normal or high pyruvate (and normal oxygen pressure) indicates mitochondrial dysfunction. With intracerebral MD, the normal upper limit for the LP ratio of the human brain has been defined as 30 [22, 24]. Increased levels of glutamate and glycerol indicate hypoxia/ischemia and have been defined as indicators of excitotoxicity and cell membrane breakdown, respectively [19].

The LP ratio obtained from MD of cerebral venous blood may be a sensitive indicator of impending cerebral damage and secondary neurological deterioration and might play a critical role in detecting the early responses of post-resuscitation care. The use of global cerebral MD may potentially aid clinicians in providing individualized and tailored brain resuscitation strategies that prevent secondary brain injury and lead to improved survival and neurological outcomes after cardiac arrest.

Our group recently reported how it is technically simple and feasible to place an MD catheter in the jugular bulb and monitor biochemical variables related to global cerebral energy metabolism at the bedside during cardiac surgery [29]. In the study, we evaluated a new method of cerebral metabolic monitoring, namely MD of cerebral venous blood drainage. The cerebral venous blood drains mainly to the jugular bulbs. Most of the outflow is to either the left or right side, depending on dominance. The study concluded that metabolic monitoring in the central venous outflow (jugular bulb) is representative of the overall cerebral metabolism and can be used in the diagnosis of compromised global cerebral metabolism during cardiac surgery.

## Methods/Design

This study is a double-blinded, randomized, superiority clinical trial assessing the effect of different blood pressure levels on global cerebral metabolism in addition to TTM in adult comatose patients resuscitated from OHCA. Patients are enrolled at one Danish university hospital with a population background of about 1.3 million citizens for highly specialized cardiac care. The SPIRIT (Standard Protocol Items: Recommendations for Interventional Trials) 2013 Checklist, together with the Statement, facilitated with drafting of the trial protocol (Additional file 1).

### Aim

The study aims are to (a) investigate whether the LP ratio obtained by MD of the cerebral venous outflow reflects a derangement of global cerebral energy state after OHCA, (b) investigate the effect of higher MAP on global cerebral metabolism and LP ratio in comatose patients resuscitated from OHCA, and (c) investigate the correlation between LP ratio and neurological outcome (cerebral performance category, or CPC). The null hypothesis is that a higher MAP will not reduce LP ratio within 48 h compared with lower MAP.

### Trial procedure

#### Phase 1 (hospital admission to intervention onset)

Comatose patients after OHCA admitted to the hospital with sustained return of spontaneous circulation (ROSC) are eligible for screening. Acute computed tomography (CT) scan or acute coronary angiogram performed before ICU admission is also included in this phase. The inclusion window is 220 min from ROSC to screening. Patients eligible for the trial must comply with all inclusion criteria according to Table 1 at randomization. In accordance with Danish legislation, if no exclusion criteria are met, proxy informed consent is obtained from next of kin and from one independent medical doctor not involved with the trial.

**Table 1 Tab1:** Inclusion and exclusion criteria

Inclusion criteria	
1. Age of at least 18 years	
2. Out-of-hospital cardiac arrest (OHCA) of presumed cardiac cause	
3. Sustained return of spontaneous circulation (ROSC), defined as ROSC when chest compressions have not been required for 20 consecutive minutes and signs of circulation persist	
4. Unconsciousness (Glasgow Coma Scale (GCS) score of less than 8) after sustained ROSC	
5. Target temperature management (TTM) is indicated.	
Exclusion criteria	
1. Conscious patient (GCS score of at least 8)	
2. Female of child-bearing potential, unless a negative human chorionic gonadotropin (hCG) test can rule out pregnancy within the inclusion window	
3. In-hospital cardiac arrest (IHCA)	
4. OHCA of presumed non-cardiac cause, such as after trauma, dissection/rupture of major artery or arrest caused by hypoxia (i.e., drowning, hanging, etc.)	
5. Known bleeding diathesis (medically induced coagulopathy does not exclude patient)	
6. Suspected or confirmed acute intracranial bleeding	
7. Suspected or confirmed acute ischemic stroke	
8. Unwitnessed asystole	
9. Known limitations in therapy and do-not-resuscitate order	
10. Known disease making 180-day survival unlikely	
11. Known pre-arrest cerebral performance category (CPC) score of 3 or 4	
12. More than 4 h (240 min) from ROSC to randomization	
13. Systolic blood pressure of less than 80 mm Hg in spite of fluid loading/vasopressor and/or inotropic medication and/or mechanical circulatory support*	
14. Temperature of less than 30 °C on admission	
15. Uncorrected blood glucose of less than 2.5 mmol/L at admission	

* If systolic blood pressure is recovering during the inclusion window the patient can be included

Enrollment of patients will be performed by the attending physician who is not involved in data collection or assessment. Randomization of blood pressure target was performed by a computerized algorithm using STATA (StataCorp LLC, College Station, TX, USA) in varying block sizes of 4, 8, and 12 patients. Baseline characteristics are obtained.

#### Phase 2 (intervention period)

OHCA patients are randomly allocated to either low- or high-blood pressure target during ICU stay: Allocation of patients resuscitated from OHCA to low- or high-blood pressure target during ICU stay):. The  first invasive blood pressure using the trial blood pressure module is marking the start of the intervention, most often coinciding with initiation of TTM. Interventions are considered emergency procedures, and study blood pressure measurement using the study blood pressure modules (HP/Philips M1006B Invasive Pressure module) is commenced as soon as possible after sustained ROSC, screening, and randomization. Study target blood pressure will be blinded. In half of the modules, the calibration factor will be adjusted in order to show the blood pressure measurements about 10% lower than the patients’ actual blood pressure at 100 mm Hg, and in half of the patients, the blood pressure measurements will be shown to be about 10% higher at 100 mm Hg. Targeting an MAP of 70 mm Hg during treatment in both groups will mean a blinded comparison of 63 and 77 mm Hg, both of which are within the usually acceptable ranges of blood pressure. A prospective, randomized, controlled clinical study has validated this method for double-blinded comparison of MAP targets in the ICU setting [30]. The intervention continues for as long as the patient has invasive blood pressure measurements.

##### Blood pressure management during ICU stay

MAP is increased by administration of (a) volume resuscitation until CVP is at least 10 mm Hg and distensibility index of the inferior vena cava is less than 12%, unless pulmonary edema is clinically apparent, and (b) norepinephrine (μg/kg per min solution) is administered in increments of 0.02 μg/kg per min until a dose of 0.2 μg/kg per min is reached. A higher dose will be used at the discretion of the attending physician; (c) dopamine (μg/kg per min solution) will be used in addition to norepinephrine at a maximal dose of 10 μg/kg per min.

As part of the routine hemodynamic monitoring, a pulmonary artery catheter (PAC) is inserted via the internal jugular or subclavian vein under ultrasound guidance. During ICU stay, cardiac index, mixed venous oxygen saturation (SvO_2_), central venous, and pulmonary pressures were measured continuously by PAC (CCOmbo PAC^®^, Edwards Lifesciences, Irvine, CA, USA) linked to the correct monitor (Vigilance II^®^, Edwards Lifesciences). These data, together with information on blood temperature, oxygen saturation, and MAP measured from a radial artery line, were transferred electronically to a computer with a 2-second time interval. If echocardiography, and thermodilution suggest that low cardiac output addition of an inotropic agent may be appropriate). The following agents may be considered: (a) milrinone (0.375–0.75 μg/kg per min) and (b) levosimendan (0.1 μg/kg per min). If an inotropic agent at maximal dose combined with vasopressors cannot maintain cardiac output, mechanical circulatory support may be considered.

##### Neuromonitoring during ICU stay

At ICU arrival, patients will be implanted with a jugular bulb MD catheter and monitored for 96 h or until arousal. MD samples are collected in microvials and analyzed every 1 h at the bedside. Regional cerebral oxygen saturation will be monitored by using bifrontal NIRS (Somanetics INVOS Cerebral Oximeter system). Right and left frontal regional oxygen saturation (rSO_2_) values will be recorded simultaneously during ICU stay, and values will be recorded every hour for 96 h or until arousal.

##### Mechanical ventilation and oxygenation during ICU stay

Patients will be mechanically ventilated, sedated, and when necessary paralyzed with neuromuscular blocking agents to reduce shivering and subsequent heat generation and energy consumption. The study is targeting normal oxygenation (13–14 kPa) during TTM and mechanical ventilation. Ventilation is adjusted, targeting normocapnia of partial pressure of carbon dioxide (paCO_2_) of 4.5–6.0 in all patients.

Serial arterial blood gas will be analyzed open-label by using commercially available equipment adjusted to 37 °C (alpha-stat). The TTM intervention period of 24 h commenced at the time of randomization by using an automated feedback device with temperature control to achieve a target core temperature of 36 °C. After TTM, patients are rewarmed to a core temperature of 37 °C with no more than 0.5 °C per hour. Phase 2 ends when sedation is withheld.

#### Phase 3 (from end of sedation to 72 h after OHCA)

Sedation is terminated after rewarming when the temperature is at least at 37 °C. Normothermia of 37 °C ± 0.5 °C is maintained until 72 h after the cardiac arrest as long as the patients are managed in the ICU and are unconscious. Nevertheless, weaning from ventilation will be attempted at the earliest possible time during this phase on the basis of typical procedures for discontinuation of mechanical ventilation. Blinded physicians perform a neurological evaluation of patients who remain in coma at 72 h or later after OHCA. The number of patients still comatose at 72 h after the end of TTM who underwent neurological prognostication will be reported. The number of patients who died before neurological prognostication and their presumed cause of death, including limitations in care and explanations for that, will be described. If judged by attending physicians to be indicated, electroencephalogram, somatosensory evoked potentials, and CT of the brain will be performed.

#### Phase 4 (end of intervention period to hospital discharge)

This starts when invasive blood pressure measurement is discontinued during the ICU stay.

Neurological outcome will be assessed at hospital discharge in accordance with the CPC scale [31, 32]: CPC 1, no neurological deficit; CPC 2, mild to moderate dysfunction; CPC 3, severe dysfunction; CPC 4, coma; and CPC 5, death. CPC scores of 1 and 2 are mostly considered “good” outcomes, and a CPC 3–4 “poor” outcomes. Physicians performing the CPC assessment will be blinded to patient’s LP ratio levels.

#### Phase 5 (hospital discharge/3 months after end of trial)

Vital status and neurological status (CPC) were evaluated at 3 months after admission by clinical examination or telephone interview. Vital status will be evaluated at the end of the trial by using the Danish civil registration system. The SPIRIT timeline of progress through the phases of the parallel-randomized trial is shown in Fig. 2.

**Fig. 2 Fig2:**
[figure not shown]
Overall schedule and time commitment for trial participants. *Abbreviations*: *CPC* cerebral performance category, *HA* hospital admission, *HD* hospital discharge, *MAP* mean arterial blood pressure, *NIRS* near infrared spectroscopy, *PAC* pulmonary artery catheter, *TTM* targeted temperature management.

### Inclusion

Patients at least 18 years old with sustained ROSC after OHCA are eligible for inclusion if complying with all the criteria presented in Table 1.

### Bedside monitoring of cerebral energy microdialysis

Patients will be implanted with a jugular bulb MD catheter (CMA 67 IV 130 mm, MDialysis AB, Stockholm, Sweden) and monitored for 96 h or until arousal. The catheter allows energy-related metabolites to diffuse into the catheter reflecting accurate concentrations in the venous blood, CE marked according to the Medical Device Directive, 93/42/EEC. MD catheters are inserted in a retrograde direction into the jugular bulb, through a peripheral intravenous 17 GA cannula by using ultrasound guidance, as performed in a previous study [29]. The positioning of the catheter tip in the jugular bulb above the inlet of the common facial vein is confirmed on cranial CT scan in accordance with earlier practice [33]. MD pumps (CMA 106, MDialysis AB) at 0.3 μL/min perfuse MD catheters. The perfusates are collected in microvials, analyzed every 1 h for minimum 96 h by enzymatic photometric techniques, and presented at the bedside (Iscus, Mdialysis AB). The analyses include the biochemical variables regularly monitored during intracerebral MD: glucose, pyruvate, lactate, glutamate, and glycerol. Clinical data, radiology, electroencephalography, somatosensory evoked potential, and NIRS will be recorded.

### Logistics

The study is enrolling at one university hospital with experience in conducting clinical trials. All investigators have been qualified and are licensed in “good clinical practice” (GCP).

### Patient and public involvement

Patients were not involved in setting the research hypothesis or end-points, nor were they implicated in the design of the study. There are no plans to include patients in the dissemination of results, nor will we publish results directly to patients.

### End-points

The study focuses on the following end-points:

Primary end-pointComparing mean LP ratio differences within 48 h between blood pressure groups and comparing individual LP ratio measurements using longitudinal analysis.

Secondary end-pointsAssociation between LP ratio and all-cause mortality during ICU stay adjusted for blood pressure groupsBetween-group difference in total duration (minutes) of cerebral desaturation defined as an absolute rSO_2_ of not more than 50% during ICU stayBetween-group difference within 48 h in lactate, pyruvate, glutamate, glycerol, and glucose measured in jugular bulbAssociation between LP ratio and cardiac index adjusted for blood pressure groupsAssociation between LP ratio and survival to hospital discharge with poor neurological function (CPC 3–4) adjusted for blood pressure groups.

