### Statistical analysis plan

The statistical analyses will be the following:Analyses will be performed in accordance with the intention-to-treat principle and will take into account patients lost to follow-up.A two-sided significance level of 0.05 will be applied to both primary and secondary end-points.Unpaired *t* tests or Mann–Whitney *U* tests will be conducted for unpaired comparisons of numerical variables. A chi-squared or Fisher’s exact test will be conducted to examine differences between categorical variables.Association between LP ratio and “poor” neurological outcome (CPC 3–4) will be assessed with chi-squared test and logistic regression. The overall expected rates of unfavorable neurological outcome (CPC 3–4) are 5–7%, observed in earlier studies [34, 35]. The multivariate logistic model will be adjusted for time to ROSC, arterial carbon dioxide partial pressure, baseline LP, and average LP ratio > 30 > 24 and 48 h as covariates.Association between LP ratio and all-cause mortality will be assessed with chi-squared test and logistic regression.Receiver operating characteristic (ROC) curves will be constructed to determine the sensitivity and specificity of the LP ratio levels at each time point (and the maximal LP ratio level recorded during the ICU period) for predicting outcomes.Association between total duration (in minutes) of cerebral desaturation (rSO_2_ ≤ 50%) and unfavorable neurological outcome (CPC 3–4) and death will be assessed with chi-squared test and logistic regression.Time from start of randomization to death in the two blood pressure groups will be assessed by using the Kaplan–Meier method, and group differences will be tested by log-rank test. Cox regression will be applied for adjusted comparisons and estimation of hazard ratios.In regard to dynamic changes of MD variables in the two blood pressure groups, longitudinal models, applying linear mixed effects regression, will be used to account for repeated measurements of MD biomarkers across different patients over time.In regard to dynamic changes of blood pressure, longitudinal models, applying linear mixed effects regression, will be used to account for repeated measurements of blood pressure across different patients over time.

All standard assumptions regarding statistical models will be checked. Statistical analysis will be performed by using STATA V.15 (StataCorp LLC).

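### The desaturation end-point is total minutes over the ICU stay, but rSO2 is recorded hourly and stops at 96 h or arousal, so the total is confounded with monitored time

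*Protocol article*

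**What the plan says.** Three places in the Protocol article matter.

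- **End-points.** One of the secondary end-points is the between-group "difference in total duration (minutes) of cerebral desaturation defined as an absolute" rSO2 of 50% or less. Its window is the ICU stay.
- **Neuromonitoring during ICU stay.** "Regional cerebral oxygen saturation will be monitored by using bifrontal NIRS". Of the right and left frontal readings it says that "values will be recorded simultaneously during ICU stay", and the same sentence goes on: "values will be recorded every hour for 96 h or until arousal". No other interval is given for rSO2.
- **Statistical analysis plan.** The same quantity is used again as a predictor: "Association between total duration (in minutes) of cerebral desaturation" is related to CPC 3–4 and to death by chi-squared test and logistic regression. No scaling to monitored time is mentioned.

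Two other statements give context. Under Blood pressure management during ICU stay, the pulmonary artery catheter data, blood temperature, oxygen saturation and MAP "were transferred electronically to a computer with a 2-second time interval"; NIRS is not in that list. In End-points, the LP ratio and the other microdialysis variables are compared within 48 h, so those comparisons have a fixed window and the desaturation end-point does not.

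**The concern.** Two mismatches stand out. The first is the unit: an end-point in minutes is to be built from one reading per side per hour. The second is the window: the end-point spans the ICU stay, while recording ends at 96 h or at arousal, which need not be when the patient leaves the ICU.

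The second matters more. A total that is not divided by monitored time is desaturation rate multiplied by exposure, and exposure here is tied to outcome. A patient who dies early or wakes early accrues few minutes; one who stays comatose accrues many. When the total is then used to predict death and CPC 3–4, part of any association reflects how long the patient was watched. The distortion may run in opposite directions: early death lowers the total, which works against an association with death, while persistent coma raises it, which inflates an association with CPC 3–4. Between the arms, randomisation does not remove the problem if the blood pressure target itself alters time to arousal or death.

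**Working it through.** The plan gives no design figure for this end-point, so there is none to reproduce. Its one design figure, 46 patients for the primary end-point, does reproduce: difference 15, SD 15, two-sided 0.05, power 0.9 gives 22.02 per arm by t-test, hence 23 per arm. It has no bearing on this point.

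**1. Resolution.** With hourly readings over at most 96 h there are at most 96 readings per side. Totals are multiples of 60 min, from 0 to 96 × 60 = 5760 min.

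**2. Bias from hourly sampling.** For a single episode of d minutes, d < 60, the chance that a reading falls inside it is d/60, and it then counts as 60 min. The expected count is (d/60) × 60 = d. A 20-min episode is missed with probability 1 − 20/60 = 2/3 and otherwise counts as 60, so on average it counts as 20. Hourly sampling is unbiased.

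**3. Noise from hourly sampling.** The chance of missing a single episode is 1 − d/60: 83% at 10 min, 50% at 30 min, 25% at 45 min. The effect on a patient's total was simulated with assumed inputs, none of which the documents give: 72 h monitored, 10% of time desaturated, and exponentially distributed episodes and gaps.

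| Mean episode | True mean (min) | Hourly estimate (min) | SD of error (min) | Correlation with truth |
|---|---|---|---|---|
| 10 min | 434 | 435 | 131 | 0.53 |
| 30 min | 439 | 445 | 86 | 0.87 |
| 120 min | 413 | 412 | 47 | 0.99 |

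At assumed burdens of 2%, 5% and 20% the correlations are similar: 0.51–0.57, 0.84–0.87 and 0.98–0.99 for the three episode lengths.

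**4. Dependence on monitored time.** Total minutes = 60 × monitored hours × fraction of time desaturated. Assume the same fraction, 10%, for everyone:

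- 72 h against 60 h: 432 against 360 min, ratio 1.2
- 72 h against 48 h: 432 against 288 min, ratio 1.5
- 96 h against 48 h: 576 against 288 min, ratio 2.0

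In each pair the percentage of monitored time is 10% for both, so the whole difference comes from exposure.

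**5. How much of the total is monitored time.** Assume monitored hours uniform on 24–96 h, mean burden 10%, and burden independent of hours. The share of between-patient variance in minutes explained by hours then depends on the coefficient of variation (CV) of burden:

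| CV of burden | Share explained by monitored hours |
|---|---|
| 0.25 | 63% |
| 0.4 | 40% |
| 0.5 | 30% |
| 1.0 | 10% |
| 2.0 | 3% |

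**6. Is exposure likely to vary?** Recording stops at arousal by design, and death ends it as well. The Background notes that "the in-hospital mortality is reported to be 30–50" percent among patients admitted to an ICU. The article does not give the distribution of monitored hours in either arm.

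**The case against.** The best defence is that NIRS is a bedside monitor and the hourly values may be charting on top of a continuous device record. The text says rSO2 is monitored as well as recorded, the schedule figure and full protocol are not shown, and the list of 2-second signals sits in a paragraph on haemodynamics, so the absence of NIRS there is weak evidence. This stands: a continuous log cannot be excluded. It would remove the unit problem but not the dependence on monitored time.

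Three stronger readings are tempting, and the documents do not support them.

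- **That the end-point cannot be measured.** Within the monitored window, 60 times the number of low readings estimates total minutes without bias, and closely if episodes are long. What the stated recording cannot deliver is minute-level duration over the whole ICU stay.
- **That the total mostly reflects monitored time.** Under the assumptions above the share runs from 3% to 63%, and it passes one half only when burden varies little between patients. The documents give no rSO2 distribution to settle it.
- **That the arms could differ several-fold.** A reader might take the earliest end of sedation, 24 h plus (37 − 36)/0.5 = 2 h of rewarming, and set 96/26 = 3.7. That compares two extreme patients, not two arms, and treats the end of sedation as arousal. Nor is 26 h a floor, since a patient may die sooner. No difference between arms in monitored time can be derived.

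It can also be said that cumulative burden is a legitimate quantity and that this is one secondary end-point, absent from the abstract's list. Both are fair and limit the weight of the point. Neither justifies an unscaled total in a model for death and CPC.

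**Conclusion.** The point holds in a limited form. As written, total minutes over the ICU stay do not match hourly rSO2 values that end at 96 h or arousal, and the unscaled total is confounded with monitored time. The confounding matters most in the association with death and CPC 3–4, because arousal and death help determine how long a patient is monitored. The between-arm comparison is biased only if the blood pressure target affects time to arousal or death, which is possible but not shown.

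The size cannot be derived from the documents. The twofold difference at 96 h against 48 h rests on an assumed equal 10% burden and shows the mechanism only. The loss from hourly sampling ranges from negligible to serious with episode length, which is not given. The primary end-point and the sample size are unaffected.

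**What to change.** In End-points and in the Statistical analysis plan section, replace total minutes during the ICU stay with the percentage of monitored time at rSO2 of 50% or less within a fixed window. The 48 h already used for the LP ratio and metabolites is the natural choice. If the oximeter keeps no continuous log, use the proportion of hourly readings at or below 50%. Use the same measure in the group comparison and in the association with death and CPC 3–4, and state the NIRS capture interval actually used.

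The change is to wording only and uses readings already being taken. It has two costs. Desaturation after the window becomes descriptive. Patients who die or wake within the window still contribute fewer readings, so the number of readings per patient should be reported by arm and by outcome. Scaling reduces the dependence on monitored time but does not remove it entirely.
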